### Screening procedures, consent to participate, and enrollment

One of two screening and enrollment procedures has been applied, depending on the modality of first contact with potential candidates for the project. When contacted by telephone by teenagers having heard of the project and interested in participating, researchers summarize the study, and a meeting is scheduled to complete screening procedures, sign the consent forms, and complete pre-intervention measures. When participants are recruited directly on site, screening, consent, enrollment, and pre-intervention measures are completed immediately. Participants are informed of the possibility of a delay (a few weeks up to a few months) before starting the intervention, as participants continue to be recruited. Informed consent will be obtained by all recruited participants. Intervention will begin either when: (1) 20 participants are selected to be in the experimental group; or (2) 10 participants are selected to be in the experimental group (thus implying that two experimental groups of 10 participants will be run), depending on recruitment speed and efficiency.

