### Randomization

Participants will be assigned to one of two groups according to a computer-generated randomization list (computerized random numbers). As such, participants will be randomly assigned with a 1:1 allocation ratio following permuted block design procedures, using block sizes of four. No stratification criteria will be used. The allocation sequence will be generated by an independent researcher not involved in this project after baseline measures, thus ensuring that therapists and recruiters are kept blind to the allocation of each participant. The allocation sequence will be password protected and only accessible by the independent researcher. The research assistant responsible for the logistics of this project - who is not part of the treatment team - will not be kept blind for allocation and will be responsible for contacting participants randomly assigned to the experimental condition.

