### Measures

#### Assessment time-points

Measures will be completed by all participants (that is, experimental and control group) at three moments in time: (1) baseline, after the screening interview, consent forms are signed and enrollment is confirmed; (2) immediately post-intervention, at the end of the eighth session; and (3) at 6 months follow-up, when questionnaires will be sent out by mail. At each time period, participants will fill out the questionnaire package, taking approximately 60 min to complete. There will be time allocated at the first and last sessions to complete questionnaires on site. After the third assessment period, once the last questionnaire package has been sent back to the research team, a $10 iTunes gift cards will be mailed to each participant to thank him/her for his/her participation. All measures and corresponding assessment time-points are illustrated in Figure 
2.

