## Trial status

This is a clinical trial with ongoing patient recruitment. Recruitment for this project started in September 2012, and is expected to be completed by May 2013. This trial is recorded under the number NCT01783418.

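### Baseline is measured at enrolment but session 1 waits for a group to fill, so the pre-post change tested first also counts a variable waiting period

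*Protocol article*

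**What the plan says.** **Baseline at enrolment.** Under Screening procedures, consent to participate, and enrollment, people who telephone are given an appointment: "a meeting is scheduled to complete screening procedures, sign the consent forms, and complete pre-intervention measures". For the others, "When participants are recruited directly on site, screening, consent, enrollment, and pre-intervention measures are completed immediately". Assessment time-points agrees, opening its list of three assessments with "1) baseline, after the screening interview, consent forms are signed and enrollment is confirmed". The Randomization section has the allocation sequence generated after baseline.

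**A later start.** The screening section starts the intervention once 20 participants, or alternatively 10, are in the experimental group. It adds: "Participants are informed of the possibility of a delay (a few weeks up to a few months) before starting the intervention".

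**Questionnaires at session 1.** Assessment time-points also states: "There will be time allocated at the first and last sessions to complete questionnaires on site". The last session matches the post-intervention assessment. The first session matches none of the three listed assessments.

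**The analysis.** Planned statistical analyses tests change across baseline, 8 weeks and 6 months. It puts the intra-group evaluation under the primary hypotheses and the comparison with wait-list controls under the secondary ones. The Primary aim section likewise words the expected benefit as improvement from before to after the intervention in the experimental group.

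**The concern.** A pre-post change estimates an intervention effect only as far as nothing else moves the score between the two measurements. Here the first measurement can precede session 1 by months, and that gap is part of the estimate.

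In this population the gap is unlikely to be neutral. The trial does not select on type, stage or trajectory of cancer, and the Discussion expects worsening health and the start or restart of treatment during the study. The instruments look back over short periods: two weeks for the Beck scales, a few weeks for the PANAS-C, and a month for quality of life and sleep. A package completed several months before session 1 describes a period that may have little to do with the participant's state when the intervention begins. Recovery or decline in between would be credited to, or held against, the meditation programme.

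Two smaller matters follow. An older baseline may be a weaker covariate in the ANCOVA, which the plan relies on for power. And the session-1 questionnaire time leaves room for a second baseline that exists only in the experimental arm, because controls attend no sessions in this phase.

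**Working it through.** The plan states no figure for the wait beyond its own wording, so there is none to reproduce. The size can be gauged from its recruitment figures.

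**Inputs from the protocol article**
- 40 participants (Participants).
- 1:1 allocation in blocks of four, so two experimental participants per block (Randomization).
- Start when 10 or 20 are in the experimental group (screening section).
- "Recruitment for this project started in September 2012, and is expected to be completed by May 2013" (Trial status), that is, 8 to 9 months.
- Eight weekly sessions, with the second assessment at the close of session 8.

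**Assumptions**
- Accrual is uniform over the window.
- Session 1 takes place on the day the last experimental participant of the group enrols. Any set-up time would lengthen the wait.

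**Step 1: spacing of enrolments.** The window W is 8 × 30.4375 / 7 = 34.8 weeks, or 39.1 weeks for 9 months. With 40 uniform enrolment times the expected gap is W / 41 = 0.848 or 0.954 weeks.

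**Step 2: positions in the enrolment order.** Within a block of four, the two experimental places fall on average at 5/3 and 10/3. The first experimental participant is therefore expected at place 1.67.
- One group of 20: last at 36 + 3.33 = 39.33, average place 20.5. Mean wait is 39.33 − 20.5 = 18.83 gaps; longest is 39.33 − 1.67 = 37.67 gaps.
- Two groups of 10 (first group shown, second alike): last at 16 + 3.33 = 19.33, average place 10.5. Mean wait is 8.83 gaps; longest is 17.67 gaps.

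**Step 3: weeks from baseline to the post-intervention visit** (wait plus about 8)

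| Start rule | Mean wait | Longest wait | Mean interval | Longest interval |
|---|---|---|---|---|
| One group of 20 | 16.0–18.0 | 32.0–36.0 | 24–26 | 40–44 |
| Two groups of 10 | 7.5–8.4 | 15.0–16.9 | 15.5–16.4 | 23–25 |

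Each range runs from the 8-month to the 9-month window. A simulation of 10,000 recruitments under the same assumptions gave the same values. In it the interval exceeded 12 weeks for 84–86% of experimental participants with one group of 20, and for 68–71% with two groups of 10.

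**Step 4: without the accrual assumption.** Taking only the article's own description of the delay, a wait of 3 weeks gives an interval of 11 weeks (11/8 = 1.4 times the label). A wait of 13 weeks gives 21 weeks (21/8 = 2.6 times).

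**Step 5: which analysis is affected.** In the within-group test the wait enters the estimate directly. Between arms, participants are randomised after baseline, so the wait is balanced in expectation provided controls are assessed on the same dates. The balance fails only if one arm's baseline is taken at a different time.

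**The case against.** The sections on screening, randomisation and assessment agree that baseline follows consent and precedes allocation. The session-1 sentence does not call itself a baseline, and the figure of measures and time points, which might settle its purpose, is not available here. The 8-week label can be read as the name of a visit, since Assessment time-points ties that visit to the last session and nothing models elapsed time from baseline. The option of groups of 10 shortens the wait. This is also a pilot, and Pilot study endpoints already records the time each step takes. All of that stands. It does not remove the waiting period from the within-group change, and documenting the delay is not the same as handling it in the analysis.

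A reader might infer three stronger points, which the document does not support.
- *That the randomised comparison is biased.* This would need an experimental-arm-only baseline. The session-1 sentence permits that reading but does not state it.
- *That allocation is predictable*, because it is made "following permuted block design procedures, using block sizes of four". Guessing later assignments requires knowing earlier ones. The Randomization section keeps recruiters and therapists blind and gives only the independent researcher access to the sequence.
- *That a definite share of the information is lost through an older covariate.* If the baseline-to-post correlation fell from 0.7 to 0.5, residual variance would rise by 0.75 / 0.51 = 1.47. If it fell only to 0.65, the ratio would be (1 − 0.65²) / 0.51 = 1.13. The article gives no correlation, and participants enrolled just before a start wait hardly at all, so no figure can be attached.

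**Conclusion.** The point holds as a weakness of the within-group pre-post test. Baseline is fixed at enrolment, the start rule makes a wait unavoidable for all but the last to join each group, and the plan tests this change first. The interval labelled 8 weeks averages about 15.5 to 16.4 weeks with two groups of 10 and 24 to 26 weeks with one group of 20, given uniform accrual over the stated window. On the article's words alone it is about 8 weeks plus a delay of weeks to months, unequal between participants.

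The direction and size of the resulting distortion cannot be stated, because they depend on how scores drift during the wait. Some loss of strength in the baseline covariate is plausible but cannot be quantified. Bias between arms is conditional on how the session-1 questionnaires are used.

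**What to change.** **Participants not yet allocated.** Define one baseline for both arms. When a cohort is full (20 enrolled for a group of 10, or 40 for a group of 20), all its members complete the questionnaire package shortly before session 1, on matched dates. The independent researcher releases that cohort's allocations only afterwards. State that a questionnaire completed at session 1 is not used as a baseline for the experimental arm alone.

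**Participants already allocated.** A repeat measure would come after allocation, so it should not replace the covariate in the randomised comparison.
- Keep the enrolment measure, taken before allocation, as the ANCOVA covariate.
- Repeat the package in both arms in the week before session 1 and use it as the starting point for the pre-post change.
- Record each participant's interval from enrolment to session 1 for use in the analysis.

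**Cost.** At most one extra 60-minute package per participant, which matters somewhat in a trial that names attrition as a limitation. Families also get short notice of allocation before eight weekly sessions begin. Neither the sample size nor the intervention changes.

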### Literature review and rationale

As previously mentioned, individuals living with cancer are at risk for significant psychological distress
[3,4,9]. Approximately 20% to 30% of individuals with cancer manifest depressive symptoms of clinical significance
[10]. Moreover, chronic physical symptoms, such as sleep disorders and fatigue, tend to appear consequently to cancer treatments; approximately 85% of individuals with cancer suffer from sleep disorders
[11,12].

Recent studies have shown a positive impact of MBSR on psychological health in individuals with cancer. Specifically, a recent meta-analysis has indicated moderate effect sizes of mindfulness meditation on stress, anxiety, depression, quality of life, sleep, and fatigue related to cancer, highlighting the predominant role this practice can play in the individual’s psycho-social adaptation
[9]. Research has also shown both immediate and 1-year post-intervention positive impacts of the practice on stress, quality of life, and mood in the same population
[11,13,14]. Furthermore, the group setting in which MBSR takes place has been shown to decrease isolation and loneliness often observed in the context of cancer, therefore promoting better relationships and stronger social support, which, in turn, may explain improvements in mood and quality of life
[15].

Altogether, authors have concluded that mindfulness meditation has beneficial effects on physical and psychological symptoms among adults with different chronic illnesses, and could hence be a key tool in the treatment of these conditions
[16,17]. Emerging research in pediatrics is suggesting similar effects in children and adolescents
[18-21]. The few studies that have examined its effects on youth with chronic illnesses tend to suggest that mindfulness meditation acts similarly by decreasing physical and emotional pain
[22].

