### Participants

Based on prior studies testing cognitive-behavioral interventions in adolescents with cancer, eligible participants are adolescents aged 11 to 18 years with a diagnosis of cancer
[23-25]. In keeping with previous research, there will be no specific selection/exclusion based on type, stage, or trajectory of cancer
[11,26-28]. The intervention will be conducted in French. Therefore, participants are required to speak and understand the language. They must be willing to participate in an 8-week mindfulness meditation program and be available to complete the measures 6 months after the intervention. They must not have a diagnosis of severe mental illness.

Based on prior mindfulness intervention studies with adolescent populations and on usual number of participants in a mindfulness-intervention training group (as indicated by Kabat-Zinn and colleagues
[29] in the MBSR program) a final sample size of 28 participants is targeted
[13,29-33]. Taking into consideration attrition rates from prior research (20-30%), an additional 12 participants will be recruited
[2,34-36]. Thus, a total of 40 participants will be recruited. Participants will be randomly assigned to the experimental or control group, and immediately given a participant ID for confidentiality and anonymization purposes. Twenty adolescents will be completing the mindfulness meditation intervention, which will be taught by two trained therapists (doctoral clinical psychology student and psychiatrist). The intervention will comprise of eight weekly sessions, lasting 90 min each.

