### Wait-list

The use of a wait-list control condition has been compelling in past studies on MBSR and cancer to test for the effectiveness of the intervention without compromising recruitment, while favoring retention of participants who will later benefit from the intervention
[36,37]. Once the follow-up assessment has been completed with the experimental group, wait-list controls will be offered to complete the mindfulness-based program. The data collected on these participants through the second round of intervention will also be analyzed to test the mindfulness-based intervention.

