### Experimental group

The present mindfulness-based meditation intervention is inspired by protocols designed at the Centre de consultation psychologique specialisé of the Université Catholique de Louvain (Belgium)
[38], as well as by Biegel and colleagues
[39]. The intervention will be led by two trained therapists (psychologist and psychiatrist), alternating roles (leader *vs.* co-leader) at each session, leading a total of four sessions each. In accordance with the initial MBSR program designed by Kabat-Zinn and colleagues
[5], the mindfulness-based intervention will last 8 weeks, the group meeting once a week and each session lasting 90 min. Based on previously cited protocols designed for youth, no silent retreat will be included in this intervention.

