### Planned statistical analyses

Descriptive statistics on participant characteristics will be presented for each group at baseline. Means and standard deviations on primary and secondary outcome variables will be presented for each group at 8 weeks and 6 months.

The cut-point to reject the null hypothesis will be set at 5% (α ≤0.05). Primary hypotheses will first be tested using three mixed analyses of covariance (ANCOVA) with Bonferonni corrections and individual critical alpha levels at 1.67% (α ≤0.0167), that will allow comparison of data at each time-point
[54]. The use of mixed ANCOVAs will help reduce within-group error variance, namely by controlling for baseline differences between participants in each condition and by taking into account possible confounds (for example, age, diagnosis, cancer stage), while providing a higher statistical power in detecting an intervention effect (
[55,56]).These intra-group analyses will serve to evaluate the impact of the mindfulness-based meditation intervention on quality of life, sleep, and mood pre-post intervention, as well as follow-up.

Specifically, changes in quality of life scores (as indicated by the Pediatric Cancer Quality of Life Inventory) between baseline, 8 weeks and 6 months will be tested. Similarly, a change in sleep quality scores (as indicated by the Pittsburgh Sleep Quality Index) and mood scores (as indicated by the Depression and anxiety scales of the Beck Youth Inventories and the PANAS-C) will be tested between baseline, 8 weeks and 6 months. These analyses will also serve to test secondary hypotheses, by allowing inter-group comparisons between the experimental group and the wait-list controls. Specifically, a difference in quality of life scores, sleep quality scores, and mood scores at baseline, 8 weeks, and 6 months will be assessed between groups.

Comparable analyses will be conducted on the data collected from the second experimental group once participants from the wait list condition go through the intervention. All statistical analyses will be conducted using SPSS version 20 (SPSS Inc., Chicago, IL, USA).

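### The experimental arm is treated in one or two groups, but the ANCOVAs treat its members as independent, so the tests exceed their nominal 1.67% level if outcomes within a group are correlated

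*Protocol article*

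**What the plan says.** **Delivery.** Under Screening procedures, consent to participate, and enrollment, the article gives two ways to start: "Intervention will begin either when: (1) 20 participants are selected to be in the experimental group", or a start at 10, "thus implying that two experimental groups of 10 participants will be run". Under Participants: "Twenty adolescents will be completing the mindfulness meditation intervention, which will be taught by two trained therapists". The Experimental group section has the same pair lead all eight weekly sessions, with "the group meeting once a week and each session lasting 90 min".

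**Controls.** Under Wait-list: "Once the follow-up assessment has been completed with the experimental group, wait-list controls will be offered to complete the mindfulness-based program". Randomization is individual and 1:1, so only the experimental arm is clustered during the comparison.

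**Analysis.** Under Planned statistical analyses: "Primary hypotheses will first be tested using three mixed analyses of covariance (ANCOVA", each at a Bonferroni level of 1.67%. The pre-post and follow-up changes are the primary, intra-group analyses, and the between-arm comparison serves secondary hypotheses. Adjustment is for baseline and possible confounds, with age, diagnosis and cancer stage as examples. The wait-list round is to be analysed in a comparable way.

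**Expected group influence.** The Literature review and rationale section says that "the group setting in which MBSR takes place has been shown to decrease isolation and loneliness often observed in the context of cancer", and offers this as a possible explanation of better mood and quality of life. The Process measure section adds social support scales to see whether gains can be traced to the social side of the program.

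**The concern.** Adolescents who share eight sessions, the same peers and the same therapists are likely to have correlated outcomes. The plan itself names the mechanism. An analysis that counts them as independent uses too small a standard error for any statement about the intervention in general. The "mixed" in the ANCOVA refers to time-points and arms. It does not bring in a treatment-group effect, and the analysis, power and discussion sections contain no variance adjustment or limitation for shared groups.

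Two things are at stake. The tests would reject more often than the 1.67% that the Bonferroni correction is meant to secure. And with one group, that group's own effect, including its therapists', is fully confounded with the intervention effect. With two groups, the between-group variance rests on one degree of freedom, so no later model can estimate it usefully.

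**Working it through.** **Inputs from the article.** Final sample 28, recruited 40, allocation 1:1, one group of 20 or two of 10, overall alpha 5%, three tests. **Assumed.** ICC 0.01, 0.05 and 0.10 for the quantity tested; two-sided tests; independent controls; equal total variance in both arms; losses spread evenly over arms and groups.

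**The plan's own figures.** 0.05 / 3 = 0.0167, as stated. 28 / (1 − 0.30) = 40, as stated. So 28 / 2 = 14 completers per arm, giving m = 14 per treatment group with one group and m = 7 with two.

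**Variance factors.** The design effect in the experimental arm is DEFF = 1 + (m − 1) × ICC.

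- Intra-group change: the SE should be multiplied by √DEFF.
- Between-arm contrast, equal arms, only one arm clustered: by √[(DEFF + 1)/2] = √{[2 + (m − 1) × ICC]/2}.

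| m | ICC | DEFF | Between-arm factor | Intra-group factor |
|---|---|---|---|---|
| 14 | 0.01 | 1.13 | 1.03 | 1.06 |
| 14 | 0.05 | 1.65 | 1.15 | 1.28 |
| 14 | 0.10 | 2.30 | 1.28 | 1.52 |
| 7 | 0.01 | 1.06 | 1.01 | 1.03 |
| 7 | 0.05 | 1.30 | 1.07 | 1.14 |
| 7 | 0.10 | 1.60 | 1.14 | 1.26 |

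**Error rates.** These come from simulated trials with no true effect, 200,000 per cell, tested at 1.67%. A two-sample t-test stands in for the between-arm contrast, and a one-sample t-test on change stands in for the intra-group contrast. Repeat runs agree to about 0.1 percentage point. At ICC 0 both tests return 1.67%.

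| Groups | ICC | Between-arm | Intra-group |
|---|---|---|---|
| One of 14 | 0.01 | 2.0% | 2.3% |
| One of 14 | 0.05 | 3.8% | 5.8% |
| One of 14 | 0.10 | 6.3% | 11.0% |
| Two of 7 | 0.01 | 1.8% | 2.0% |
| Two of 7 | 0.05 | 2.5% | 3.3% |
| Two of 7 | 0.10 | 3.6% | 5.5% |

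**Check without simulation.** With one group, the one-sample t statistic is a t variable on 13 degrees of freedom multiplied by √[DEFF/(1 − ICC)]. At ICC 0.05 that is √(1.65/0.95) = 1.318. The 1.67% critical value is 2.745, and 2.745/1.318 = 2.083. The two-sided tail beyond 2.083 on 13 degrees of freedom is 5.8%, which matches.

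**If all 20 per arm are analysed.** At ICC 0.05 the between-arm error is 4.8% with one group and 3.0% with two. The intra-group error is 8.2% and 4.4%.

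**Does the SE factor repair it?** Applied at the true ICC, it brings the between-arm error back to about 1.7% to 2.0%. The intra-group test with one group returns to 1.7%, 1.9% and 2.2%. The small remainder arises because clustering also shrinks the SD observed within a group.

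**The case against.** **This is a pilot with open details.** The covariate list is given by example, and a clustering sensitivity analysis could sit in an analysis plan that is not shown. That much is fair. But the article fixes both the delivery and the tests, and no covariate can repair the one-group option, because a group term there coincides with the arm. The feasibility endpoints are unaffected, and that limits the weight of the point.

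**The ICC is unknown.** This stands. The article makes a positive correlation plausible but says nothing of its size. A reader might infer that the error rate is certainly far above nominal. The documents do not support that: at ICC 0.01 it is 1.8% to 2.3%.

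**Confidence intervals.** A reader might infer that the planned intervals are too narrow. The article names none. It plans means, SDs, p-values, partial eta squared and Cohen's d. The same SE would affect any interval built from these models, but that is not something the plan commits to.

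**Overgeneralisation.** A reader might infer that results will be presented as holding beyond these groups. The article does not say so. Its Discussion limits generalisation to adolescents of similar motivation and health, and the Pilot study endpoints section speaks of potential benefit. Neither mentions the group or therapist effect, however, and that is the gap.

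**Accuracy of the factor.** It assumes equal arms and rescales a single contrast, whereas the mixed ANCOVA also yields F tests with several degrees of freedom. It is an approximation, adequate for a sensitivity range.

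**Conclusion.** The point holds, with a size that depends on an assumed ICC. Individual randomization with group delivery in one arm only, analysed as independent, exceeds the nominal 1.67% for any positive ICC. With 14 completers per arm and ICC 0.01 to 0.10, the between-arm test runs at about 2.0% to 6.3% with one group and 1.8% to 3.6% with two. The intra-group tests that the article makes primary run at about 2.3% to 11.0% and 2.0% to 5.5%. So the excess ranges from slight to more than six times nominal (11.0/1.67 = 6.6). Independently of the ICC, one or two groups cannot separate group or therapist effects from the intervention effect. This limits the weight of the hypothesis tests and effect sizes. It does not invalidate the pilot, and the documents give no basis for making significance conditional on any particular ICC.

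**What to change.** In Planned statistical analyses, add a sensitivity analysis over ICC 0.01 to 0.10, with m the mean number of participants analysed per treatment group:

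- Multiply the SE of each between-arm contrast by √{[2 + (m − 1) × ICC]/2} if the arms are equal. Otherwise inflate only the experimental arm's variance, by 1 + (m − 1) × ICC.
- Multiply the SE of each intra-group change by √[1 + (m − 1) × ICC], and do the same for the later wait-list round.
- If two groups are run, show experimental-arm results by treatment group.

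In the same section and in the Discussion, state that one or two groups cannot separate the group or therapist effect from the intervention effect, so the p-values and effect sizes are exploratory.

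The cost is a small amount of extra analysis, a sentence or two of text, and less favourable p-values. No added participants or change of design are needed, and the article reports recruitment as ongoing.
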